#### Secondary Analysis

Each of the components of the primary outcome, death and rehospitalization, will be analyzed separately as described for the primary outcome. Time to death and rehospitalization after 30 days and 1 year will be analyzed by fitting Cox proportional hazards regression models with trial arm as explanatory variable. Hazard ratios including their confidence intervals will be reported. Patients will be censored on their last known follow-up. To illustrate the course of deaths and re-hospitalizations in the two treatment arms, a Kaplan-Meier Curve will be presented.

Length of hospital stay will be calculated in days considering index and each rehospitalization separately and by the sum of all hospital stays. Standard summary statistics for numerical data will be performed. If distribution of data allows, significant differences of mean of length of hospital stay between arms will be assessed with a *t*-test (two-sided α = 5%). If distribution is skewed, data will be transformed or other models selected.

The secondary outcomes (falls, fractures, course of hyponatremia, recurrence of hyponatremia, severe symptomatic hyponatremia, overcorrection of hyponatremia) will be analyzed as described for the primary outcome. To account for multiple occurrences of falls, fractures, and recurrence of hyponatremia after 1 year, we will apply a Poisson model.

Diagnostic performance of biomarkers will be assessed by calculating sensitivity, specificity and accuracy as well as best cut-offs. Gold standard is the correct diagnosis of etiology of hyponatremia, which is expert opinion based on biochemistry results and treatment response.

Analyses of differences of quality of life score and of executive functioning score between arms will be performed also considering grade of hyponatremia and its correction. Multivariate linear models will be used to explore possible associations.

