
Episodes of overcorrection (defined as increase >12 mmol/l/24 h, respectively 18 mmol/l /48 h) and their complications will be recorded. Targeted plasma sodium correction will be maintained—for a maximum of 30 days—until normonatremia is achieved or when the patient is discharged from hospital. At discharge the last available plasma sodium level and whether or not patient was treated according to protocol will be recorded. Not treated according to protocol applies in the case treatment recommendation is not implemented or the patient does not adhere to the prescribed treatment (details see below “Compliance with study intervention”). In case of hospitalization exceeding 30 days, the last plasma sodium level before stopping the intervention (day 31) will be recorded as the discharge plasma sodium. Treatment after discharge will not be influenced by the study team, however a treatment recommendation and request to monitor plasma sodium levels will be given to the general practitioner in the discharge letter.

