##### 2. Treatment

Treatment of hyponatremia will be solely at the discretion of the attending physicians. The study team will not intervene with the treatment in any way. Treatment decisions as well as the course of the plasma sodium level will be recorded after patient is discharged from hospital using the medical records and patient charts. To ensure the planned outcome assessment, it will be generally recommended to measure plasma sodium levels 3 times weekly or more frequently if clinically indicated, before discharge and after 30 days.

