#### Primary Analysis

Analysis of the primary outcome will follow the intention-to-treat principle. It will be based on the full analysis set. To test whether the study intervention differs from standard care 30 days after randomization, the Pearson's χ^2^-test without Yates's correction will be applied. Threshold for rejecting the null hypothesis will be α = 5%. The estimated absolute difference between study arms will be reported alongside its 95% confidence interval.

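### The course of hyponatremia is assigned the primary outcome's unadjusted chi-square test; a baseline-adjusted mean difference in sodium should be added to show how far the arms separated.

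*Protocol article*

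**What the plan says.** The Secondary Analysis section groups "course of hyponatremia, recurrence of hyponatremia, severe symptomatic hyponatremia" with falls, fractures and overcorrection, and says that these "will be analyzed as described for the primary outcome". The Primary Analysis section says that Pearson's chi-square "test without Yates's correction will be applied" and adds: "The estimated absolute difference between study arms will be reported alongside its 95% confidence interval". It names no covariates.

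No other between-arm method is named for sodium. The Poisson model covers repeated falls, fractures and recurrence at 1 year. The t-test is for length of stay. The linear models are for quality of life and executive functioning.

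Sodium is recorded as a number. In the intervention group: "At discharge the last available plasma sodium level and whether or not patient was treated according to protocol will be recorded". For stays beyond 30 days, the last value before the intervention stops at day 31 is used instead. In the control group: "Treatment decisions as well as the course of the plasma sodium level will be recorded after patient is discharged from hospital", and "it will be generally recommended to measure plasma sodium levels 3 times weekly or more frequently if clinically indicated, before discharge and after 30 days". Entry requires a value below 130 mmol/l (Table 1), so every patient has a baseline value. The article refers to Supplementary Table 2 for the full set of outcomes; that table is not shown.

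**The concern.** A chi-square test reported as an absolute difference compares two proportions. Applied to sodium, it needs a yes/no version such as normal or not normal at discharge, and it leaves out the entry value.

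Two statements in the Discussion make this matter more than it would for a routine secondary outcome. The limitations paragraph expects that, because of early discharge and non-compliance, sodium will rise in a number of patients without becoming normal. A split at normonatremia counts these patients the same as patients with no rise. The closing paragraph says that a null result on death and rehospitalization would shift opinion towards hyponatremia as a marker of disease severity. That reading depends on how far the arms actually separated in sodium. A mean difference in mmol/l answers this directly; a difference in proportions answers it only at one threshold.

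**Working it through.** **1. The plan's own figure.** The article gives no figure for the sodium outcome, so the sample size only supplies the number per arm. Inputs (Determination of Sample Size): 23% against 18%, two-sided 5%, 80% power, 10% drop-out.

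- n per arm = [1.96·√(2·0.205·0.795) + 0.842·√(0.23·0.77 + 0.18·0.82)]² / 0.05² = 1023, so 2046 in total against the stated 2050.
- 2050 / 0.90 = 2278, as stated.

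The sample size is sound and does not depend on this point. The rest uses 1025 per arm.

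**2. Information kept by a split.** For a roughly normal outcome, a small shift between arms, and a proportion p on one side of the cut c, relative efficiency = φ(c)² / [p(1−p)].

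| p on one side | Efficiency against comparing means |
|---|---|
| 50% | 0.64 |
| 70% | 0.58 |
| 75% (or 25%) | 0.54 |
| 80% (or 20%) | 0.49 |

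The 25% row is illustrative. The Background cites a registry in which up to 75% were still hyponatremic at discharge, and that is an upper limit.

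**3. Against a baseline-adjusted analysis.** Adjustment multiplies the residual variance by (1 − r²), where r is the correlation of baseline with last sodium. The article does not give r, so a range is shown, at 25% normonatremic:

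- r = 0.2: 0.54 × 0.96 = 0.52
- r = 0.4: 0.54 × 0.84 = 0.45
- r = 0.6: 0.54 × 0.64 = 0.34

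**4. What this does to power.** The sodium shift is assumed, in SD units, because the article gives neither a shift nor an SD. The split column covers 25%, 50% and 70% of controls above the cut; the adjusted column covers r = 0.3 to 0.7.

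| Shift | Means, unadjusted | Chi-square on split | Means, baseline-adjusted |
|---|---|---|---|
| 0.10 SD | 62% | 39-44% | 66-89% |
| 0.125 SD | 81% | 56-62% | 84-98% |
| 0.15 SD | 92% | 72-77% | 94-99.7% |
| 0.20 SD | 99.5% | 92-95% | above 99% |

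The loss is material for small shifts and minor from about 0.20 SD upward.

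**The case against.** The endpoint's definition is not visible. The neighbouring items in the same sentence are mostly events, and the control-group wording about the course of sodium describes data capture rather than an endpoint. A reader might infer that the plan forces a defined continuous endpoint into a test that cannot handle it, and so contains an error. The documents do not support that: Supplementary Table 2 may define normalization yes/no, and the chi-square test would then be valid.

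A binary endpoint also has merit. The intervention itself aims at normonatremia, and overcorrection raises a mean without being a success. At this sample size a proportion is well estimated: with 25% in each arm, the 95% half-width is 1.96·√(2·0.25·0.75/1025), about 3.7 percentage points. A shift too small for the split to detect would itself suggest that the intervention moved sodium very little.

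The figures are approximate. Restricting entry to values below 130 mmol/l tends to lower r, and stopping correction at normonatremia strains the normal model.

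The replacement has weaknesses of its own. The last sodium is taken at a time that treatment may affect, some patients die before discharge, and control measurements are only recommended.

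These points rule out calling the plan wrong, and they rule out replacing the binary endpoint. They do not remove the case for adding the mean difference. A proportion at one cut still does not show partial correction, which the article expects, and baseline sodium is available but unused.

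**Conclusion.** The point holds as an efficiency and interpretation improvement for one secondary outcome. The stated method is valid if the endpoint is binary. It keeps roughly 49-64% of the information in a roughly normal sodium measure for cuts with 20-80% on one side. At 25% normonatremic it keeps about 0.52 to 0.34 of what a baseline-adjusted analysis uses, for r between 0.2 and 0.6. The 25% and the correlations are assumptions.

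Two further inferences go too far. One is that the randomized sodium comparison would be biased; an unadjusted test of a binary endpoint is not biased for being unadjusted or binary. The other is that a null primary result could not be interpreted at all without this change; if the sodium separation is 0.20 SD or more, the split would very probably show it. What would be missing is a direct estimate of the separation in mmol/l.

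**What to change.** Add to the Secondary Analysis section a linear regression of the last sodium before discharge (or before the intervention stops at day 31) on arm, baseline sodium and site, the last being the stratification factor. Use the same definition in both arms and report the mean difference in mmol/l with its 95% confidence interval. Keep the proportion normonatremic, with its chi-square test, as a separately named companion endpoint. For patients who die before discharge, use the last available in-hospital value. Report time from randomization to the last sodium by arm.

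The cost is a few sentences, with no new measurements and no change to the primary analysis or sample size. This is a cheap improvement rather than a free one: discharge timing varies and may be affected by treatment, and reporting the timing by arm shows that problem but does not remove it.

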### Sample Size Calculations and Statistical Analyses

#### Determination of Sample Size

Sample size was estimated based on our already completed observational multi-center study in 298 patients with profound hyponatremia (37, 38). The study showed a 30-day mortality rate of 6.4% and a 30-day rehospitalization rate of 18.5%. Of the re-hospitalized patients, ~2% died and thus were counted twice. We therefore propose a combined event rate of 23% under standard care. Our systematic review identified only one study that investigated the impact of targeted correction of hyponatremia on mortality and rehospitalization (25). In this observational study, an absolute reduction of the combined event rate of 7.1% (33.7 vs. 26.6%) was reported. Through our intervention, we expect to achieve an absolute risk reduction for mortality and rehospitalization of 5 %. Sample size was calculated for a Pearson's χ^2^-test. We set 80% power for a two- sided test with an α error of 5%. A drop-out rate of 10% was assumed. In order to have 2050 evaluable patients, 2,278 patients must be recruited.

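### The 1-year Poisson model for repeat falls, fractures and recurrences makes no stated allowance for clustering within patients or for unequal follow-up; any rehospitalisation-only curve should treat death as a competing event

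*Protocol article*

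**What the plan says.** All the analysis wording is in the Protocol article, Secondary Analysis.

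- Repeat events: "To account for multiple occurrences of falls, fractures, and recurrence of hyponatremia after 1 year, we will apply a Poisson model". No dispersion term, robust variance or exposure time is mentioned.
- The sentence before it lists secondary outcomes, including falls, fractures and recurrence, and ends "overcorrection of hyponatremia) will be analyzed as described for the primary outcome". Under Primary Analysis that means a Pearson chi-square test with an absolute difference and its 95% confidence interval.
- Time to event: "Time to death and rehospitalization after 30 days and 1 year will be analyzed by fitting Cox proportional hazards regression models", with trial arm as the explanatory variable. The censoring rule is "Patients will be censored on their last known follow-up".
- Display: "To illustrate the course of deaths and re-hospitalizations in the two treatment arms, a Kaplan-Meier Curve will be presented". Death is not named as a competing event for rehospitalisation.
- For length of stay, the same section provides a fallback (transformation or another model) if the data are skewed. The repeat counts get none.

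**The concern.** The reason given for the Poisson model does not support it. Its model-based variance equals its mean, so a patient's events are treated as if they carried no information about that patient's underlying risk. Falls or recurrent hyponatremia that concentrate in frail patients break that assumption. The article itself makes clustering plausible: under Study Intervention it describes the population as highly heterogeneous, and the subgroups range from stroke to malignancy to surgical diagnoses. If the variance exceeds the mean, standard errors are too small and chance differences are declared significant more often than 5% of the time.

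Exposure time is a second gap. Planning mortality is 6.4% by day 30 and the assumed drop-out is 10%, while counts run for a year. The trial hopes to reduce mortality. If it does, intervention patients are observed for longer and can accrue more events, and an analysis without an offset would compare counts over unequal time.

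A related matter concerns the curves. If rehospitalisation is plotted alone with deaths censored, one minus Kaplan-Meier estimates readmission as if nobody died, which exceeds the proportion actually readmitted.

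**Working it through.** **The plan's own figures.** The article gives no figure for these secondary analyses. Its sample size reproduces and is not affected. With 23% against 18%, two-sided 5% and 80% power, the number per arm is [1.960 × √(2 × 0.205 × 0.795) + 0.842 × √(0.23 × 0.77 + 0.18 × 0.82)]² / 0.05² = 1,023, or 2,046 in total (stated: 2,050). Then 2,050 / 0.90 = 2,278, as stated.

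**Poisson test under overdispersion.** Let the mean count be μ and the variance μ + kμ², so the variance/mean ratio is φ = 1 + kμ. A Wald test on the log rate ratio with model-based standard errors understates the true standard error by a factor √φ. Its true two-sided type I error is 2 × [1 − Φ(1.96/√φ)]. Both μ and k are assumptions. The simulated column uses gamma-Poisson counts, 1,025 per arm (half of 2,050), 20,000 runs.

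| μ | k | φ | Formula | Simulated |
|---|---|---|---|---|
| 0.1 | 0 | 1.00 | 5.0% | 4.8% |
| 0.1 | 0.5 | 1.05 | 5.6% | 5.6% |
| 0.1 | 2 | 1.20 | 7.4% | 7.6% |
| 0.3 | 1 | 1.30 | 8.6% | 8.4% |
| 0.3 | 2 | 1.60 | 12.1% | 12.3% |
| 0.5 | 2 | 2.00 | 16.6% | 16.8% |
| 1.0 | 2 | 3.00 | 25.8% | 25.9% |

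**Kaplan-Meier at 30 days, on the article's rates.** Determination of Sample Size states: "The study showed a 30-day mortality rate of 6.4% and a 30-day rehospitalization rate of 18.5" (per cent), and "Of the re-hospitalized patients, ~2% died and thus were counted twice". Read as percentage points, 6.4 + 18.5 − 2 = 22.9%, which matches the planned 23%. Deaths without readmission are then about 23 − 18.5 = 4.5%; 6.4% is the upper bound.

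Let r be the proportion readmitted and d the proportion dying first. With constant cause-specific hazards, the total cumulative hazard is L = −ln(1 − r − d), the readmission share is L × r/(r + d), and one minus Kaplan-Meier is 1 − exp(−L × r/(r + d)).

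- r = 18.5%, d = 4.5%: L = 0.2614, share 0.2102, result 19.0% (+0.5 points).
- r = 18.5%, d = 6.4%: L = 0.2864, share 0.2128, result 19.2% (+0.7 points).

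**Kaplan-Meier at 1 year, on assumed rates.** With r = 40% and d = 15%, 25% or 30%, the same formula gives 44.1%, 47.6% or 49.7% (+4 to +10 points).

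A second set of assumptions starts from yearly hazards h_r (readmission) and h_d (death). Cumulative incidence is h_r/(h_r + h_d) × [1 − exp(−(h_r + h_d))], and one minus Kaplan-Meier is 1 − exp(−h_r).

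- h_r = 0.5, h_d = 0.15: 36.8% against 39.3% (+2.6 points).
- h_r = 0.7, h_d = 0.25: 45.2% against 50.3% (+5.1 points).
- h_r = 0.7, h_d = 0.35: 43.3% against 50.3% (+7.0 points).

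Together the two sets give roughly 3 to 10 points.

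**The case against.** The strongest reply is that the article is a condensation. It says a Poisson model, not one with model-based errors. Robust variance, a dispersion check and an offset are commonly left to the analysis plan, which is not shown, and nothing in the article excludes them. That stands as a reason to word the point conditionally. It does not remove it, because the article presents the model as the means of handling repeat events, and the model alone does not do that.

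Three stronger inferences are tempting and are not supported.

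- **That p-values for falls, fractures and recurrence will be too small.** These outcomes are also compared by chi-square, with one binary value per patient, which repeat counts cannot distort. The Poisson analysis supplements that. For rare events such as fractures the inflation may be slight: 5.6% to 7.4% at a mean of 0.1 with k from 0.5 to 2.
- **That the plan overstates readmission risk.** The single Kaplan-Meier curve is illustrative and may show the composite, where death is an event and this bias does not arise. The time-to-event comparison is by Cox model; fitted to rehospitalisation with deaths censored, it gives a valid cause-specific hazard ratio. Only its label is missing.
- **That the separate chi-square on rehospitalisation is wrong because a patient who dies first counts as not readmitted.** The plan says "Each of the components of the primary outcome, death and rehospitalization, will be analyzed separately as described for the primary outcome". With complete 30-day follow-up, the proportion readmitted is the cumulative incidence, the same quantity that Aalen-Johansen estimates, and deaths are reported beside it.

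It is also fair that all patients share a 1-year contact, so omitting an offset does not by itself bias the null comparison when mortality and follow-up are equal between arms.

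**Conclusion.** The point holds in conditional form and is limited to secondary analyses. Taken literally with model-based errors, the 1-year Poisson analysis is anti-conservative if events cluster within patients: about 6% to 26% in place of 5% for variance/mean ratios of about 1.05 to 3, and no inflation at a ratio of 1. The direction is certain given overdispersion; the size rests wholly on assumed means and dispersions. The missing offset matters if death or drop-out differs between arms.

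The Kaplan-Meier remark applies only if rehospitalisation is drawn alone. It is then small at 30 days (0.5 to 0.7 points on the article's rates) and could be material at 1 year (roughly 3 to 10 points, on assumed rates). The primary test, the sample size and the chi-square comparisons are untouched.

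**What to change.** 1. For 1-year counts of falls, fractures and recurrences, replace the Poisson model with negative binomial regression, or with Poisson regression using robust variance. In either case include the log of follow-up time as an offset.
2. State whether the Kaplan-Meier curve shows death, the composite or rehospitalisation. Keep Kaplan-Meier for the first two. For rehospitalisation alone, draw Aalen-Johansen cumulative incidence with death as a competing event.
3. Label the rehospitalisation Cox estimate as a cause-specific hazard ratio and report it beside the hazard ratio for death.

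The cost is a few lines of analysis-plan wording and standard software; no new data or patients are needed. Intervals widen by a factor of about √φ: roughly 2% at a ratio of 1.05, 41% at 2 and 73% at 3. Recruitment stood at 750 of 2,278 when the article was written, so the wording could be settled before results by arm are seen.

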1. **Diagnosis:**Diagnosis of hyponatremia will be made by the local study physician and will be reviewed by the local principal investigator. According to the *ECPG*, patients will be classified into the 3 main groups of hypotonic hyponatremia (decreased/normal/increased extracellular fluid volume; details see Supplementary Figure 1). If the diagnosis is uncertain, the most likely categorization will be chosen. This initial diagnosis can and shall be changed according to treatment response and/or additional clinical information. The final diagnosis will be made before the patient is discharged.2. **Treatment:**The proposed treatment recommendation will be based on the predefined algorithms which were developed in accordance to the ECPG(2) and the EPR(3) (details see Supplementary Figure 2). The treatment algorithm is a recommendation only, meaning the proposed algorithm is intended as a guideline rather than a strict treatment plan. This approach takes into account the sometimes limited data for certain treatments (36) and enables the local expert to decide upon the best treatment for every patient individually based on the available treatment options. Given that the hyponatremia patient population in clinical practice is very heterogeneous, we decided a tailored approach for hyponatremia correction would be in the best interest of the patients. Except for correction of hyponatremia, the local study team will not influence other treatment goals and decisions, which will be fully at the discretion of the attending physicians. Treatment response and adherence will be evaluated daily. The study nurse will report to the study physician, who will additionally examine the patient if clinically indicated. The study physician will then—under the supervision of the local principal investigator—adapt treatment recommendation according to the predefined treatment goals and inform the treating physicians about the treatment modification. The general treatment goal is to raise plasma sodium levels by at least 2 mmol/l/24 h. These treatment goals also define the time until the next treatment step should be implemented. The following management rules apply:increase ≥2 mmol/l/24 h and <12 mmol/l/24 h and 18 mmol/l/48 h: current treatment option will be maintained until plasma sodium level has normalizedincrease <2 mmol/l/24 h: treatment will be intensified or switched to a different modalityincrease >12 mmol/l/24 h and/or 18 mmol/l/48 h: treatment will be discontinued and, if needed, counter regulatory actions (i.e., hypotonic infusion, administration of desmopressin) will be administered according to the decision of the local principal investigator.

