Even though randomized controlled trials are considered the best study design to assess causality, some limitations of our trial should be mentioned. First, this trial takes place in a real-world setting, so logistical obstacles and reduced adherence to recommended treatment may occur. Non-compliance by both the treating physician and/or the patient may compromise the number of patients in the per protocol analysis. Also, full hyponatremia correction may not be achieved in patients who are quickly discharged. More specifically, we take into account that both premature discharge and non-compliance will affect the number of patients in which full hyponatremia correction can be realized. As a consequence, in a number of patients plasma sodium concentration is expected to increase but not reach normal levels within the hospitalization period. Early discharge can especially limit the chance of successful hyponatremia correction in patients who require treatment escalation or sequential use of various treatment options. Yet, results from this trial will be a good reflection of everyday clinical practice. Second, we anticipate that this trial may increase the overall awareness for hyponatremia in the study centers which may lead to improved hyponatremia management in the control group. However, the problem of contamination is not expected to be significant enough to warrant a cluster-randomization design. Also, cluster-randomization designs are much more susceptible to selection bias and therefore do not outweigh the advantages of individual randomization (60). Third, to avoid contamination, the study team will not order diagnostic tests in the control group. As a result, the etiology of hyponatremia in the control group will be derived from the combination of all available clinical and laboratory findings and treatment response. Follow-up plasma sodium measurements in the control group will be recommended because this is necessary to ensure the planned outcome assessment. We acknowledge that this creates an area of tension between possibly contaminating standard of care and complete data collection to address the primary research question.

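### Biomarker cut-offs are to be chosen from data with no stated correction for the choice, so reported sensitivity would be too high, most for rare aetiologies

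*Protocol article*

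**What the plan says.** The biomarker analysis takes two sentences of the protocol article's Secondary Analysis section. The first gives the method: "Diagnostic performance of biomarkers will be assessed by calculating sensitivity, specificity and accuracy as well as best cut-offs". The second gives the reference standard: "Gold standard is the correct diagnosis of etiology of hyponatremia, which is expert opinion based on biochemistry results and treatment response".

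Two other places bear on how many patients could contribute:

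- The Intervention Group section says that "patients will be classified into the 3 main groups of hypotonic hyponatremia (decreased/normal/increased extracellular fluid volume" is the basis of classification. It does not say how many patients are expected in each group or aetiology.
- The Discussion says that, "to avoid contamination, the study team will not order diagnostic tests in the control group". The Control Group section leaves laboratory work-up there to the attending physician.

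The article names no marker, target aetiology, rule for what makes a cut-off best, threshold fixed in advance, or step that would correct or validate a threshold taken from the data.

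**The concern.** A best cut-off is found by trying many thresholds and keeping the one that scores highest. The highest score owes something to real discrimination and something to chance in that sample. If sensitivity and specificity are then quoted at that threshold in the same patients, the chance part is counted as performance and will not recur in new patients.

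The smaller of the two groups being separated carries most of the noise. For a rare aetiology that is the group of cases, so the excess falls on sensitivity. At stake is whether a reported cut-off performs as stated when it is next used. The randomised comparison is not involved.

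**Working it through.** **1. The plan's own figure.** The article sizes only the primary outcome. The inputs, from Determination of Sample Size, are "We therefore propose a combined event rate of 23% under standard care", an absolute reduction of 5 points (so 18%), 80% power, two-sided 5%, and "A drop-out rate of 10% was assumed". With mean proportion 0.205 and pooled variance under the null:

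n per arm = [1.960 × √(2 × 0.205 × 0.795) + 0.842 × √(0.23 × 0.77 + 0.18 × 0.82)]² / 0.05² = (1.119 + 0.480)² / 0.0025 ≈ 1,023.

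That is 2,046 in total, against the stated 2,050. Then 2,050 / 0.9 = 2,278, as stated. The figure reproduces, but it says nothing about the biomarker analysis. It serves here only to set sample sizes to try: 2,050 evaluable patients, and 1,025 as roughly one arm.

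**2. Simulation inputs (all assumed, because the article gives none).** One marker, distributed N(d, 1) in cases and N(0, 1) in non-cases, with d = √2 × Φ⁻¹(AUC). The cut-off maximises the Youden index. Optimism is the apparent value in the sample minus the true value at the chosen cut-off. There were 600 replicates per setting. The full grid covered 200 to 2,050 patients, 2% to 40% prevalence, and AUC 0.7 to 0.9.

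**3. Results, in percentage points (AUC 0.7 / AUC 0.8).**

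| Patients | Prevalence | Cases | Sensitivity | Specificity | Accuracy |
|---|---|---|---|---|---|
| 2,050 | 40% | 820 | 0.9 / 0.9 | 0.6 / 0.4 | 0.7 / 0.6 |
| 2,050 | 20% | 410 | 1.6 / 1.4 | 0.3 / 0.4 | 0.6 / 0.6 |
| 2,050 | 2% | 41 | 7.6 / 6.1 | 0.1 / 0.1 | 0.3 / 0.2 |
| 1,025 | 40% | 410 | 1.4 / 1.2 | 1.0 / 0.8 | 1.1 / 1.0 |
| 1,025 | 10% | 102 | 4.3 / 3.3 | 0.2 / 0.3 | 0.6 / 0.6 |
| 1,025 | 5% | 51 | 6.4 / 5.9 | 0.3 / 0.2 | 0.6 / 0.5 |
| 1,025 | 2% | 20 | 11.3 / 9.2 | 0.1 / 0.1 | 0.3 / 0.3 |
| 500 | 10% | 50 | 6.4 / 4.9 | 0.6 / 0.5 | 1.1 / 1.0 |
| 200 | 40% | 80 | 4.0 / 3.6 | 2.1 / 1.9 | 2.9 / 2.5 |
| 200 | 10% | 20 | 9.8 / 8.7 | 0.9 / 0.8 | 1.8 / 1.6 |

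Sensitivity optimism depends mainly on the number of cases.

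**4. Why accuracy behaves differently.** Accuracy = prevalence × sensitivity + (1 − prevalence) × specificity, and its optimism is weighted the same way. For 2,050 patients and AUC 0.7:

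- at 40%: 0.4 × 0.9 + 0.6 × 0.6 = 0.72 points;
- at 2%: 0.02 × 7.6 + 0.98 × 0.1 = 0.25 points.

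The large error in sensitivity gets almost no weight when cases are rare, so accuracy optimism falls.

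**5. Cross-check on the Youden index.** A separate simulation with 1,500 replicates per setting gave the following:

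| True AUC | Cases / non-cases | Apparent index | True index at that cut-off | Difference |
|---|---|---|---|---|
| 0.5 | 50 / 500 | 0.089 | 0 | 0.089 |
| 0.5 | 350 / 650 | 0.040 | 0 | 0.040 |
| 0.7 | 50 / 500 | 0.342 | 0.275 | 0.067 |
| 0.7 | 350 / 650 | 0.309 | 0.284 | 0.025 |

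The direction and size agree with step 3.

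**The case against.** The strongest objection is scope. This is a condensed article, the full protocol and any SAP are not shown, and internal validation of a secondary cut-off is the kind of detail often left to them. The article never says in so many words that thresholds and performance come from the same patients. That stands as a limit: same-patient scoring is the natural reading of the sentence, not its text. But the sentence does commit to searched thresholds alongside their performance. It can be carried out as it stands, and the result would then be optimistic.

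The second objection is size. If the targets are the three volume groups and each is common, 1,025 or more patients would leave an excess in sensitivity of roughly 0.7 to 2.5 points (20% to 40% prevalence, AUC 0.7 to 0.9). That also stands. The bias becomes material at roughly 50 cases or fewer, or in a small biomarker subset, and the article establishes neither.

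A reader might infer more than this:

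- **That specificity and accuracy are also overstated most for rare aetiologies.** Steps 3 and 4 show the reverse.
- **That accuracy should be dropped because calling everyone negative scores 500/550 = 91% with 50 cases.** Such a rule has sensitivity 0 and Youden index 0, and the plan reports sensitivity beside accuracy, so the reader would see the failure.
- **That having several markers multiplies the bias.** The optimism of each marker does not grow because others are reported. That would need selection of the best marker, which the plan does not describe.
- **That the cut-offs would steer clinical classification.** The article's Objectives section does not mention biomarkers.

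**Conclusion.** The point holds as a modest one about a secondary analysis. Scored in the patients used to choose the threshold, apparent sensitivity and the Youden index would be too high, most for rare aetiologies. At a true AUC of 0.7 to 0.8 the excess in sensitivity is about 1 to 2 points with 350 or more cases, 5 to 6 with 50, and 9 to 11 with 20. For specificity and accuracy it is about 1 point or less with 1,025 or more patients, reaching 2.9 points for accuracy only in the smallest sample tried (200), and it shrinks with rarity.

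These sizes rest on normal markers of equal variance, a Youden rule, and assumed case numbers. That fewer than all patients will have biomarker data is plausible from the control-arm testing policy but is not stated. The primary test, the sample size and the safety analysis are untouched.

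**What to change.** In the Secondary Analysis section, add that each marker's AUC will be reported with its 95% confidence interval, and that any cut-off derived from trial data will carry bootstrap optimism-corrected sensitivity and specificity, with the cut-off search repeated in every resample. An alternative is to derive cut-offs in some sites and validate them in the others. The Ethics Statement lists nine centres, so this is possible, but it divides the cases and so suits rare aetiologies less well. Accuracy can stay.

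If the full protocol or SAP already contains such a step, one clause referring to it is enough.

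The cost is a little analysis code and slightly less favourable figures. No new patients or data are needed.
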